**[name]**

**[name]**

**[name]**

**[name]**

**[name]**

**[name]**

**[name]**

## Abstract

*Background:* The prescription of drugs without evidence is a significant public health problem. It can also result in large efficiency losses in the use of public resources. The aim of this study will be to test the effectiveness of a behavioral intervention based on social norm feedback to reduce non-recommended prescription of nimodipine as a drug for cognitive impairment in Argentina.

*Methods:* We will perform a pragmatic randomized trial of peer comparison feedback delivered through e-mails to high nimodipine-prescribing general practitioners (GPs) of the national health-care system for older adults (INSSJP-PAMI). Eligible GPs will be randomized to a treatment or to a control condition. The intervention group will receive two e-mails with evidence-based information about nimodipine plus the participant's level of prescription of nimodipine compared to their peers. The control arm will receive also two e-mails with general information about the risks of over-prescription and about the risk of overuse of benzodiazepines in older adults. The primary outcome will be the cumulative number of nimodipine prescriptions per 1000 prescriptions of all drugs made by the targeted practitioners during 6 months after the intervention started.

*Discussion:* The results of this study could have several potential implications for improving the quality of medical practice and public policy in the health area. It would provide an efficient tool for aligning nonrecommended prescription with the evidence and for reducing unnecessary costs without employing coercive methods and preserving the practitioners' freedom to choose. Besides, the trial would allow to test the cross-cultural validity of the social norms feedback procedure and the feasibility of implementing it via e-mail.

**Trial registration:** The trial is intended to be registered at the ISRCTN registry.

## Keywords:

nimodipine – peer comparison – nudge – behavioral insights – older adults – medication overuse

## Administrative information

|                                                         |                                                                                                                                                                                                                                                                                                                                                                                         |
|---------------------------------------------------------|-----------------------------------------------------------------------------------------------------------------------------------------------------------------------------------------------------------------------------------------------------------------------------------------------------------------------------------------------------------------------------------------|
| Title {1}                                               | Effect of social norm feedback e-mails on high-prescribers of Nimodipine in older adults: a randomized controlled trial                                                                                                                                                                                                                                                                 |
| Trial registration {2a and 2b}.                         | The trial is intended to be registered at the ISRCTN registry.                                                                                                                                                                                                                                                                                                                          |
| Protocol version {3}                                    | February 2019                                                                                                                                                                                                                                                                                                                                                                           |

## Introduction

### Background and rationale {6a}

The prescription of drugs without evidence is a significant public health problem. In the case of people over 65 years, polypharmacy and adverse effects could have negative consequences for health and quality of life. Also, undue prescriptions cause burdensome costs to the health system without any benefit for the patient. Among the medications improperly prescribed in the population of older adults, there is a diverse set of drugs used for the treatment of patients with mild cognitive impairment and dementias, including antioxidants, nootropic agents, vitamins, biological products and vasodilators (Rojas et al., 2010; Rojas et al., 2013). Currently 46.8 million people live with dementia across the world, and this number is expected to double every 20 years, reaching an estimated number of people living with dementia as high as 131.5 million by 2050 (Prince et al., 2015). The only worldwide recommended pharmacological treatment for different dementias are the acetylcholinesterase enzyme inhibitors (donepezil, galantamine and rivastigmine), and the NMDA receptor antagonist memantine (NICE, 2018; McKeith et al., 2017; Schmidt et al., 2015). In the case of Mild Cognitive Impairment, a pre-dementia syndrome, there is no recommended drug for its treatment (Petersen et al., 2018).

Previous reports in Argentina revealed that the prescription of recommended drugs for the treatment of cognitive impairment accounted for between 54 and 59% of total indications, meanwhile non-recommended drugs represented between 41 and 45 %. Among these, the most used drug was nimodipine (Rojas et al., 2010, 2013). According to the current evidence, nimodipine has a single indication for the treatment of acute subarachnoid hemorrhage, which is usually administered for short periods during the hospitalization period. There is not enough evidence for the use of nimodipine in the prevention or treatment of cognitive impairment on an outpatient and prolonged basis.

Earlier studies have shown behavioral interventions known as “nudges” can reduce inappropriate drug prescribing among physicians. Specifically, some studies employed social norm comparison, an approach that intends to modify prescribing behavior by comparing physicians’ prescriptive performance with that of their peers (Hallsworth et al., 2015; Meeker et al., 2016; Sacarny et al., 2018). The comparison against a social norm has an important influence on individual’s behavior and has been proved to be successful for modifying specific behaviors in diverse areas of public policy (John, Sanders, & Wang, 2014). Although social norm feedback has been tried in the health area as an effective tool in other world regions, no large-scale randomized controlled trials of behavioral interventions have been carried in Latin America for improving inadequate prescription

patterns by physicians (Sanders, Snijders, & Hallsworth, 2018). Also, most previous studies employed physical paper letters to deliver the messages, the question of how this type of treatment affects behavior when delivered through e-mail has been largely unexplored. This question is especially relevant from a policy point of view, especially in developing countries, where operational and budget constraints could be stringent. Communications through physical mailing may be difficult to implement and replicate at large scale (Liao & Navathe, 2018). In contrast, e-mail interventions are inexpensive and easily scaled, hence they could be a useful alternative to modify prescriptive patterns of physicians at national scale. However, some authors suggest that e-mail communications may be less effective than paper letter communications (John, Sanders, & Wang, 2014). Third, some concerns have been raised about the possible deterrence effects of feedback letters in previous studies that included strong language and that implied potential punitive actions from regulatory agencies (Liao & Navathe, 2018). The use of coercive wording or allusions to potential punishments from authorities may have obscured the mechanisms of the intervention turning difficult to separate the social norm effect from a potential deterrence effect.

## **Objectives {7}**

The main aim of this study will be to test the effectiveness of a social norm feedback intervention to reduce the unnecessary prescription of nimodipine by general practitioners within the National Institute of Social Service for Retired and Pensioners (INSSJP-PAMI) in Argentina. As secondary objectives, we will address four additional issues. First, we will assess the effectiveness of e-mails as delivering method of the behavioral intervention. Second, we will evaluate the validity of social norms feedback as a procedure for changing physicians prescriptive practice in the Latin American context. Third, given concerns about possible deterrence effects of communications with strong language or implying potential punitive actions from regulatory agencies, our intervention separates social norm and potential deterrence effects avoiding the use of coercive wording and obviating any mention to potential punishments from authorities. Fourth, we are also interested in knowing more about the acceptability of the intervention from the participants' point of view. For this purpose, a brief post-intervention survey will be implemented. We hypothesize that the treated group will reduce their rates of nimodipine prescriptions in comparison with the control group. We also expect that the intervention will be cost-effective and well accepted by the participants.

139 **Trial design {8}**

140 Pragmatic parallel group randomized controlled trial with two arms (1:1 allocation ratio).

141

142

143 **Methods: Participants, interventions and outcomes**

144 **Study setting {9}**

145 The study will be entirely carried at the National Institute of Social Services for Retired and  
146 Pensioners (in Spanish, Instituto Nacional de Servicios Sociales para Jubilados y Pensionados,  
147 INSSJP). The INSSJP was created in 1971 with the objective of providing universal coverage of  
148 social and health services to the specific needs of the retired and pensioners of Argentina. The  
149 INSSJP is the largest health insurance agency in Argentina and South America, with 5.089.021  
150 affiliates in 2015. Approximately, 65% of the Argentinean citizens older than 60 years old are  
151 affiliates of the INSSJP.

152

153 **Eligibility criteria {10}**

154 The initial study population will be the general practitioners of the INSSJP-PAMI system who  
155 prescribed at least one package of nimodipine during the last quarter of 2018 (n = 8965). The  
156 sample under study will be the high prescribers within that population, defined as the top 25%  
157 prescribers of nimodipine during the last quarter of 2018.

158

159 **Who will take informed consent? {26a}**

160 As in previous similar studies (Hallsworth et al., 2015; Sacarny et al., 2018) the present trial will  
161 not require informed consent from prescribers, since obtaining consent would invalidate the results.  
162 The study did not involve contact or direct intervention on patients, nor access to their personal  
163 information.

164

165 **Additional consent provisions for collection and use of participant data and biological  
166 specimens {26b}**

167 Not applicable

168

169

170

171 **Interventions**

172 **Explanation for the choice of comparators {6b}**

173 The control condition is conceived as a non-specific placebo comparator that replicates the format  
174 of the treatment intervention without its active ingredients (evidence-based information about  
175 nimodipine plus peer comparison). The comparator is supposed to control for non-specific  
176 behavioral factors such as receiving attention or raising awareness about over-prescription as a  
177 general problem in medical practice. Also, the placebo e-mails will allow to check if both groups  
178 open the e-mails at similar rates.

179

180 **Intervention description {11a}**

181 During the intervention phase of the study, participants in the two arms of the trial will receive two  
182 e-mail communications. The messages will be framed as a communicational campaign for  
183 improving the quality of pharmacological practice. In the case of the treatment arm, the first  
184 communication will include two components: a) evidence-based information about the adequate use  
185 of nimodipine and b) the participant's level of prescription of nimodipine compared to their peers.  
186 The second message, 3 months later, will include information on nimodipine prescriptions' change  
187 observed by the participant during the previous quarter ("change" or "no change"). The e-mail  
188 directed to those that reached a relative reduction of 10% of prescriptions compared to their  
189 baseline average will include an acknowledgement of their success intended to work as a verbal  
190 reinforcement of the positive behavior ("acknowledgement version"). The e-mail to the rest of  
191 participants will intend to potentiate the social norm component by stating that many of their  
192 colleagues reduced their prescriptions of nimodipine after the first e-mail and by encouraging them  
193 to revise their prescriptive practice ("encouragement version"). In the two modalities, the evidence-  
194 based information about nimodipine will be repeated. In the case of the control arm, the first  
195 message will contain general information about the inconveniences of unnecessary drug  
196 prescription and polypharmacy in older adults and links to medical guidelines to improve the  
197 prescription. Three months later, a second e-mail with information about the risks and  
198 complications of the use of benzodiazepines in older adults will be sent to the control group.  
199 Communications by e-mails will avoid any coercive or intimidating wording and they will  
200 purposively obviate any mention to potential punishments from authorities. Moreover, the expected  
201 change in prescriptive behavior will be framed as a free medical decision.

202

203

**Criteria for discontinuing or modifying allocated interventions {11b}**

Not applicable.

**Strategies to improve adherence to interventions {11c}**

The e-mailing system provides an estimation of how many participants open the e-mail, therefore we will consider this estimate as a proxy of the reach of the intervention. Accordingly, non-adherence could be understood as the omission of reading the e-mails. For our primary analysis, we decided to carry out an intention-to-treat approach integrating both the participants who opened the e-mail and those who did not. As a secondary subgroup analysis, we considered separately those participants that opened the e-mail. We have no plans for increasing the opening of the e-mails during the trial.

**Relevant concomitant care permitted or prohibited during the trial {11d}**

Not applicable

**Provisions for post-trial care {30}**

Not applicable

**Outcomes {12}**

The primary outcome will be the cumulative total number of nimodipine prescriptions per 1000 prescriptions of all drugs made by the targeted practitioners during the 6 months after the intervention started.

As secondary outcome, we will estimate the annual monetary savings attributable to our intervention at the national level (for details see Statistical Methods section). Also, we will perform a sub-sample analysis of the physicians that open the e-mails, as informed by the mailer system. Finally, we will assess the acceptability of the intervention through a brief *ad hoc* survey to the intervention arm participants at the end of the study (six months after the start of the intervention).

**Participant timeline {13}**

The number of nimodipine prescriptions for each physician is registered monthly during a year prior to the first e-mail (baseline period) and during the semester after (intervention period).

Follow-up period will eventually comprise a year after the intervention period ends.

**Sample size {14}**

To calculate our minimum sample size, we used GPower 3.1. Power calculation estimated a sample size of 1030 participants for detecting an effect size of  $d=0.05$ , with 80% of statistical power and a significance level of 0.05 in the repeated measures ANOVA.

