**Statistical methods**

**Statistical methods for primary and secondary outcomes {20a}**

The primary outcome will be analyzed using a mixed effects repeated measures ANOVA model. Comparisons between groups will be made using one-way ANOVA, while a multiple linear regression analysis will be implemented to evaluate the predictive value of the group condition controlling for baseline prescription levels. Finally, the Pearson chi-square test will be employed to analyze categorical variables.

To estimate the annual monetary savings attributable to our intervention at the national level, we will make the following calculations: first, we will estimate the number of items that would have been prescribed in the absence of the treatment. This number corresponds to the multiplication of the treatment effect times the number of items prescribed by an average physician in the control group during one year. We then multiply this quantity by the direct average price of each item (in U\$S), according to the registers of the INSSJP-PAMI. This gives an estimated benefit per-physician/year. Should this intervention be implemented for all eligible physicians in the country during a year, *the total estimated benefit* is projected as the product between the benefit per-physician/year and the total number of doctors included in the study in both groups. As opposed to other similar interventions (such as Hallsworth et al., 2016) we will not incur in any substantial per-physician cost, as we will implement our treatment via e-mail instead of post mail. The main cost would thus be related to the analysis of the data to retrieve the top 25% of high-prescribers and the design of the letter. Being conservative, we budget as *total estimated cost* two full-time weeks of work (as we sent two communications) of a public servant for these tasks according to national statistics. Finally, the total estimated cost-benefit of the intervention is the *total estimated benefit* minus the *total estimated cost*.

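### The claim that 1030 GPs detect d=0.05 with 80% power is not supported for the primary comparison unless baseline and outcome correlate at about 0.96, which the protocol neither states nor justifies

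*Protocol*

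**What the plan says.** Sample size {14} of the protocol states: "To calculate our minimum sample size, we used GPower 3.1". Its target is d=0.05, for which it reports: "Power calculation estimated a sample size of 1030 participants for detecting an effect size of" this magnitude. The power claim is attached to a named analysis: "with 80% of statistical power and a significance level of 0.05 in the repeated measures ANOVA". The section does not give the number of measurements, the correlation between them, the effect tested (between, within or interaction), or how d was converted to the effect size the software uses.

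Trial design {8} describes a "Pragmatic parallel group randomized controlled trial with two arms (1:1 allocation ratio").

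Outcomes {12} defines a single value per GP: "The primary outcome will be the cumulative total number of nimodipine prescriptions per 1000 prescriptions of all drugs", accumulated over the 6 months from the start of the intervention.

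Statistical methods {20a} says: "The primary outcome will be analyzed using a mixed effects repeated measures ANOVA model". The next sentence reads: "Comparisons between groups will be made using one-way ANOVA, while a multiple linear regression analysis will be implemented", the regression being adjusted for baseline prescribing.

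Eligibility criteria {10} starts from GPs who "prescribed at least one package of nimodipine during the last quarter of 2018 (n = 8965"). Recruitment {15} removes those above the 97.5th percentile, takes the top 25% of the rest, and randomises all who are still providers with an active e-mail address.

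**The concern.** A standardised difference of 0.05 is very small, and 1030 participants is a modest number for it. In a plain two-arm comparison of one value per person, d=0.05 needs more than ten times as many. The repeated measures ANOVA could close that gap only through correlation between measurements, and no correlation is stated. Cohen's d is also not the effect size that the repeated-measures routine takes; it takes f. In an interaction test, f is not d/2.

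At stake is how the result is read. If the protocol says the trial can see 0.05 SD, a null result may be taken as evidence against an effect of that size. That reading is sound only if the claimed sensitivity is real for the comparison the trial reports.

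**Working it through.** **Inputs from the protocol.** N = 1030 (515 per arm at 1:1), d = 0.05, power 80%, α = 0.05 (taken as two-sided), initial population 8965, outlier cut at the 97.5th percentile, top 25%. The correlations, numbers of occasions and f values below are assumptions, because the protocol gives none.

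**1. Reproducing 1030.** For a group-by-time interaction with two groups, m occasions, common correlation ρ and sphericity, the noncentrality is λ = f²·N·m/(1−ρ), with (m−1) and (N−2)(m−1) degrees of freedom.
- m = 3, f = 0.025, ρ = 0.8: λ = 0.000625 × 1030 × 3/0.2 = 9.66.
- m = 3, f = 0.05, ρ = 0.2: λ = 0.0025 × 1030 × 3/0.8 = 9.66.

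Both give power 0.8003 at N = 1030 and 0.7999 at N = 1029. The figure is therefore attainable exactly. Other settings come close (for example f = 0.025, m = 6, ρ = 0.7 gives 1028), so the match does not show which settings were used.

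**2. What those f values mean as an arm difference.** With two groups, the interaction f is half the standard deviation, over occasions, of the arm difference. If the arm differences all lie between 0 and δ, that standard deviation is at most δ/2, so f ≤ δ/4.
- f = 0.025 implies δ ≥ 0.10 SD.
- f = 0.05 implies δ ≥ 0.20 SD.

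With one baseline and two follow-up occasions (differences 0, δ, δ), f = δ/√18, so δ = 0.025 × 4.243 = 0.106 or 0.05 × 4.243 = 0.212. Halving d to get f is right for a two-group main effect, but not for this interaction.

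**3. Power for 0.05 SD on the primary outcome.** This is a two-sample noncentral t on one value per GP. With baseline adjustment the effective difference is 0.05/√(1−r²).

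| r | N = 1030 | N = 2185 |
|---|---|---|
| 0 (unadjusted) | 12.6% | 21.5% |
| 0.8 | 27% | 49% |
| 0.9 | 45% | 76% |
| 0.95 | 73% | 96% |

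Unadjusted, 80% power needs about 12,560 GPs. The correlation needed for 80% is r = √(1 − N/12,560): 0.958 for 1030 and 0.909 for 2185.

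**4. GPs available.** 8965 × 0.975 × 0.25 = 2185, before the provider and e-mail checks.

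**5. Detectable difference at 80% power.** (1.960 + 0.842) × 2/√N × √(1−r²). For N = 1030 the unadjusted value is 0.175. For N = 2185 it is 0.12 unadjusted, 0.072 at r = 0.8, 0.052 at r = 0.9 and 0.037 at r = 0.95.

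**The case against.** The strongest reply is that the protocol ties its 80% to a repeated measures ANOVA, names that model for the primary outcome, and collects 12 monthly baseline and 6 monthly intervention values. An unadjusted t-test is not the claim being made, and long aggregates correlate much more strongly than single months. If monthly values had a constant correlation of 0.7, 0.8 or 0.9, the 12-month and 6-month means would correlate at 0.949, 0.970 or 0.986. A baseline-adjusted comparison at N = 1030 would then have 72%, 91% or 99.8% power for 0.05 SD of the 6-month mean. An 18-month interaction test, with the 0.05 taken in monthly SDs, gives 22%, 56% and 92% at monthly correlations of 0.5, 0.8 and 0.9. Moreover, 1030 is a stated minimum and every eligible GP is randomised.

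Much of this stands. A reader might infer that the trial's power is simply 13%, that 1030 is an arithmetic slip, or that some 12,560 GPs must be enrolled. The documents support none of these. The 13% applies only to the unadjusted comparison, 1030 is attainable in the named type of analysis, and power near or above 80% is possible if the correlation is high enough.

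Two things do not stand. Reproducing 1030 does not rescue d=0.05, because the settings that give it exactly in step 1 describe differences of at least 0.10 or 0.20 SD. And the favourable correlations are assumptions: correlation that decays over time would lower them, and at a constant monthly correlation of 0.5 power is 42% with 1030 GPs.

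**Conclusion.** The stated pair of 1030 participants and d=0.05 at 80% power is not supported for the primary comparison by anything in the protocol. For a 0.05 SD difference on the cumulative 6-month rate, power with 1030 GPs runs from about 13% unadjusted to 73% at r = 0.95, and reaches 80% only at r of about 0.96. The settings that reproduce 1030 exactly correspond to differences at least two or four times larger than 0.05 SD, so d and the interaction f appear to have been conflated. That last step is an inference, since the actual settings are not reported.

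This goes beyond missing detail, because the protocol states a sensitivity that its own inputs do not deliver. It does not show that the trial is too small: the recruitment rule may supply up to about 2185 GPs, for which r of about 0.91 would suffice. The figures assume a two-sided 5% test, equal arms, a linear baseline adjustment and roughly normal test statistics.

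**What to change.** Remove the pairing of d=0.05 with 1030 from Sample size {14}. Replace it with the detectable effect for the baseline-adjusted comparison of the cumulative 6-month rate, at the number of GPs actually randomised. Possible wording:

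*With N GPs randomised 1:1 (at most about 2185 before provider and e-mail checks), the baseline-adjusted comparison of the 6-month rate has 80% power at two-sided 0.05 for a difference of 5.60/√N × √(1−r²) SD. At N = 2185 this is 0.12 × √(1−r²): 0.12 unadjusted, 0.072 at r = 0.8, 0.052 at r = 0.9 and 0.037 at r = 0.95.*

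(5.60 = 2 × (1.960 + 0.842).) Estimate r between a baseline aggregate and a 6-month aggregate from the prescription data already held, and report it. Keep d=0.05 only if that r supports it: at least about 0.91 with 2185 GPs, or 0.96 with 1030. If a repeated-measures calculation is retained as well, state the occasions, the correlation, the effect tested, f, and the arm difference that f represents.

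The cost is one paragraph and one calculation on existing data, with no extra enrolment and no design change. The downside is that the stated sensitivity may look less favourable.
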